### **9.3.3 Analyses of secondary endpoints**

All secondary endpoints (as defined in section 8.8.2) will be compared between the three treatment groups as described above (p-values will be considered explorative). In addition to the Poisson regression model, logistic regression model, analysis of variance (ANOVA), analysis of covariance (ANOVA) and non-parametric analysis of variance will be used, according to the type of endpoint.

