## 2. STUDY OBJECTIVES

**The aim of the study is to** “To determine the *effectiveness* of 14 days nutritional supplementation (RUTF or MNP) given concurrently with the appropriate medical treatment, in children diagnosed with malaria and/or diarrhoea and/or LRTI in reducing the incidence of acute malnutrition and the incidence of the three study diseases compared to a control group.”

**The primary objective** is to determine the effectiveness of 14 days of RUTF supplementation versus no supplementation control group on the *incidence of acute malnutrition*

**Primary Hypothesis:** Supplementation for 14 days with RUTF, concurrent to appropriate medical treatment for malaria, and/or LRTI, and/or diarrhoea reduces the incidence of acute malnutrition compared to a control group during 6 months follow-up, amongst children 6-59 months of age with malaria and/or, LRTI and/or diarrhoea at time of recruitment.

**Secondary objectives** include:

Incidence of malnutrition

- i.) Determine the efficacy of 14 days MNP supplementation versus a control group and RUTF versus MNP on the incidence of acute malnutrition during 6 months follow-up,

Frequency of morbidity

- ii.) Determine the effect of 14 days supplementation on the *frequency of morbidity* (3 study diseases) during 6 months follow-up, comparing both intervention groups to the control group and comparing RUTF to MNP)

Weight changes immediately after intervention period, measured at day-14 and day-28

- iii.) Measure *mean weight change* (total change and rate (grams/kg/day) of change), comparing both intervention groups separately (RUTF and MNP) to control group
- iv.) Determine *frequency of ‘no weight gain and/or weight loss’*, comparing both intervention groups separately (RUTF and MNP) to control group
- v.) Assess if provision of 14 days of RUTF or MNP supplement promotes a sustained weight gain, measured after 28-days of follow-up, comparing both intervention groups separately (RUTF and MNP) to control group

Sub group analyses

- vi.) Children under 3 years of age at inclusion: Determine the effect of 14 days supplementation on the *incidence of acute malnutrition* and *frequency of morbidity* (3 study diseases) during 6-months follow-up, comparing children under 3 years of age to older children.

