### **8.8.2 Secondary endpoints**

Secondary endpoints include

- Number of NNO's per study group in a period of 6 months
- Time to NNO
- Number of new events of a study disease in 6 months
- Weight change at 14 days and 28 days after study inclusion, and at end of study period
- Rate of weight change (grams/kg/day) at 14 days and 28 days after study inclusion, and at end of study period
- Proportion of children not gaining weight (including losing weight), measured at day-14 and day-28 after study inclusion.
- Proportion of children developing bilateral oedema
- Mortality: overall mortality, including the three study diseases and malnutrition.
- Morbidity, including the three diseases.
- Proportion of children with a reported cough at clinical visit

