## **9. DATA ANALYSIS**

## **9.1 Sample size\***

The sample size is based on the primary hypothesis: Supplementation for 14 days with RUTF, concurrent to appropriate medical treatment for malaria, and/or LRTI, and/or diarrhoea reduces the incidence of malnutrition.

The sample size calculation is based on a combined incidence of moderate and severe malnutrition amongst children who are sick.

There are hardly studies reporting the incidence of malnutrition and no studies reporting incidence of malnutrition among sick children. Therefore for the purpose of these calculations, we assume that the incidence is estimated by dividing the prevalence of malnutrition by the period of having malnutrition times 6 months:  $= [(Prevalence / Duration\ of\ moderate\ malnutrition) * 6\ months]$

The estimated incidence for moderate and for severe malnutrition will be added to result in the incidence of negative outcome as defined as primary endpoint of this study.

The prevalence of moderate malnutrition among sick children is 15.5% and the prevalence of severely malnutrition among sick children is 7.2% according to the results if we take the survey done by MSF-OCA at February 2009.

Literature gives a duration of malnutrition (untreated) is estimated to be 7.5 months [29] and the duration of severe malnutrition is estimated at 4 months at the time of the survey. As duration of malnutrition might be different in the context of Karamoja we varied assumptions in order to use the lowest incidence as a basis for the sample size. This results in sample size that is large enough to give enough statistical power for the primary hypothesis (the sample size increases with a decreasing incidence). Increasing the prevalence of malnutrition in general or decreasing the duration of severe malnutrition (as there is treatment available) resulted in a higher incidence, but prolonging the duration of moderate malnutrition to 10 months gives a lower incidence.

Therefore the incidence is based on duration of 4 months for severe malnutrition and duration of 10 months for moderate malnutrition.

This results in an incidence of 0.201 per 6 months

Formula:  $0.201 = [(0.155 / 10 + 0.072 / 4)] * 6$

The assumed incidence rate in the control group (baseline incidence) is 0.20. A 30% reduction in the supplementation group, which is considered a clinically and operationally relevant improvement, results in an assumed incidence rate of 0.14 in each of the two interventions groups.

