A Poisson regression with a binary independent group variable with proportion of 0.5 (equal allocation ratio) using a sample of 1320 observations (i.e. 660 per group) achieves 80% power at a 0.05 significance level to detect a incidence rate ratio of at least 0.7 (i.e. incidence rates of 0.14 (intervention rate) vs. 0.2 (baseline rate)).

To account for an assumed drop-out rate of approximately 10%, 734 children will be included in each group (i.e. 2202 in total for all three groups).

The sample size estimation is based on the first two hierarchical test hypotheses (while the third hypothesis comparing RUTF with MNP for non-inferiority is considered explorative). Sample size estimations are performed with PASS 2008 (Version 08.0.13, Windows XP) and SAS version 9.2 (SAS Institute, Cary, NC, USA).

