#### **9.3.1 Primary analysis of the primary endpoint**

The primary endpoint is “negative nutritional outcome” of a child within the 6 months follow-up period as defined in section 8.8.1. The incidence rate (in formulae below referred to simply as ‘rate’) of “negative nutritional outcome” will be computed as the number of events divided by total observed person-time in each treatment group. As an “event” the first time a child reaches a negative nutritional outcome will be used. The primary analysis of the primary endpoint will be performed on the intention to treat population with no imputation of missing data.

In the primary analysis, RUTF will be compared to the control group.  
The hypotheses in this step are

$$\begin{aligned} H_0: \text{rate}_{\text{RUTF}} &= \text{rate}_{\text{Control}} \\ \text{vs.} \\ H_1: \text{rate}_{\text{RUTF}} &\neq \text{rate}_{\text{Control}} \end{aligned}$$

where  $\text{rate}_{\text{RUTF}}$  = rate of “negative nutritional outcome” in the children in the RUTF group, and  $\text{rate}_{\text{Control}}$  = rate of “negative nutritional outcome” in the children in the control group.

The comparison of rates among the treatment groups will be performed by a Poisson regression model, adjusted for nutritional status at enrolment (fixed effect) and will be performed within one model including the three intervention groups with contrasts for each two-group comparison. Tests will be two-sided with a significance level of 0.05.

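### Poisson regression is the only count regression named for study-disease episodes that can recur in a child, with no provision for overdispersion

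*Protocol*

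**What the plan says.** Section 2 of the protocol puts morbidity in the study aim beside acute malnutrition: the supplements are to reduce "the incidence of the three study diseases compared to a control group". Formally, morbidity frequency is a secondary objective. The matching endpoint in section 8.8.2 is "Number of new events of a study disease in 6 months".

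Section 9.3.1 analyses the primary endpoint by Poisson regression, adjusted for nutritional status at enrolment, with rates formed as events over observed person-time. Only the first negative nutritional outcome of a child counts. "Tests will be two-sided with a significance level of 0.05". No dispersion parameter, robust variance or child-level effect is mentioned.

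Section 9.3.3 refers back to that approach for every secondary endpoint and labels the p-values explorative. It then widens the list: "In addition to the Poisson regression model, logistic regression model, analysis of variance (ANOVA", followed by analysis of covariance and non-parametric analysis of variance. The choice is to depend on what kind of endpoint it is. No negative binomial or other overdispersed count model appears, and no model is assigned to the episode count by name. Section 9.3.5 announces a detailed SAP, which is not at hand.

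**The concern.** Poisson regression takes the variance of a count to equal its mean. For a first-event endpoint this does little harm, because each child contributes zero or one event. Episodes of three common diseases over six months can recur, and section 8.2 makes rules for repeat supplementation because they are expected to.

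Two features of the protocol point to a variance above the mean. Section 1.2 argues that a child who does not regain normal nutritional status after an illness becomes more susceptible to further infection, so episodes should cluster within children. Section 9.3.2 lists factors on which children differ (age, breastfeeding, socio-economic factors, food availability, season). These enter the model only where baseline differences call for it, so differences in risk between children stay largely unmodelled.

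If counts are overdispersed and nothing is done about it, the intervals for the morbidity comparison are too narrow. Section 1.5 links effects on malnutrition and on recurrence of these diseases to a possible change in the sponsor's outpatient protocols and to advocacy. The explorative label applies to p-values and does not correct an interval.

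**Working it through.** **1. The plan's own Poisson figure, for reference.** Inputs from section 9.1: "The assumed incidence rate in the control group (baseline incidence) is 0.20"; a 30% reduction "results in an assumed incidence rate of 0.14 in each of the two interventions groups"; "using a sample of 1320 observations (i.e. 660 per group"; and the claim that this "achieves 80% power at a 0.05 significance level to detect a incidence rate ratio of at least 0.7". The Signorini formula for Poisson regression on a binary covariate with equal groups is

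N = (z₀.₉₇₅·√V₀ + z₀.₈₀·√V₁)² / (0.20 × (ln 0.7)²),

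with V₀ = 1/(0.5 × 0.5) = 4 and V₁ = 1/0.5 + 1/(0.5 × 0.7) = 4.857. This gives N = 1,311 in total (655.3 per group) against the stated 1,320, and power at 1,320 is 80.3%. Allowing for 10% drop-out, 660/0.90 rounds up to 734 per group, as stated. The figure is reproduced. It concerns first events only, so nothing below changes it.

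**2. Recurrent counts.** Let μ be the mean number of episodes per child in six months and k the dispersion, so that Var(Y) = μ(1 + kμ). The variance-to-mean ratio is φ = 1 + kμ. Then:

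- correct standard error / uncorrected Poisson standard error = √φ
- coverage of a nominal 95% interval = 2Φ(1.96/√φ) − 1
- type I error of the nominal 5% two-sided test = 2(1 − Φ(1.96/√φ))

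The protocol gives neither μ nor k. Both are assumptions here: μ from 1 to 2 and k from 0.25 to 1, with k = 0 as the case of no overdispersion.

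For example, with μ = 2 and k = 1: φ = 3, √φ = 1.73, 1.96/1.73 = 1.13, and type I error = 25.8%.

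**3. Check by simulation.** Gamma-Poisson counts were drawn with 660 children per arm and no true difference, 4,000 runs per setting. The log rate ratio was tested with the Poisson variance and with an empirical (robust) variance. Monte Carlo standard error at 5% is √(0.05 × 0.95/4,000), about 0.3 percentage points.

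| μ | k | φ | √φ | Coverage | Type I, formula | Type I, simulated Poisson | Type I, simulated robust |
|---|---|---|---|---|---|---|---|
| 1 | 0 | 1.00 | 1.00 | 95.0% | 5.0% | 4.8% | 4.7% |
| 1 | 0.25 | 1.25 | 1.12 | 92.0% | 8.0% | 8.2% | 5.1% |
| 1 | 0.5 | 1.50 | 1.22 | 89.0% | 11.0% | 10.3% | 4.7% |
| 1 | 1 | 2.00 | 1.41 | 83.4% | 16.6% | not run | not run |
| 2 | 0.5 | 2.00 | 1.41 | 83.4% | 16.6% | 16.6% | 4.4% |
| 2 | 1 | 3.00 | 1.73 | 74.2% | 25.8% | 25.9% | 5.7% |

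The formula and the simulation agree. The robust variance restores the nominal level in every setting that was run, including the one without overdispersion.

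**4. Lower means.** If each disease is analysed separately, the mean is smaller and so is the effect. With an assumed μ = 0.3 and k = 0.5, φ = 1.15 and type I error is about 6.8%.

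**The case against.** The best defence is that the protocol does not commit itself to the error. A reader might infer that it prescribes an uncorrected Poisson model for the episode count, so that the morbidity intervals are bound to be too narrow. The text does not go that far. It never excludes a scale parameter or robust variance, and either can be used within a Poisson regression. It leaves the choice to the type of endpoint, and a rank-based comparison of per-child counts is also on the list. Variance estimation is often settled in a SAP, and one is announced. All of this stands, and it limits the point to a named method without provision for a foreseeable problem.

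It does not remove the point. The protocol is not silent: it refers all secondary endpoints back to a first-event model and lists the alternatives, and none of them is a count regression that allows overdispersion. The rank-based option gives no rate ratio.

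It is also fair to say that section 1.2 makes poor nutritional recovery, rather than illness alone, the reason for later infection. That supports clustering but does not fix its size.

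A reader might further infer that time to NNO lacks a method that handles censoring. Events over person-time already allow for censoring if the rate is roughly constant, so no such request is made.

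**Conclusion.** The point holds in a limited form. Poisson regression is the only count regression that section 9.3.3 offers for a recurrent endpoint, it is carried over from an analysis of first events, and the protocol's own reasoning makes overdispersion likely. For assumed means of 1 to 2 episodes and variance-to-mean ratios of 1.25 to 3, an uncorrected analysis would have a type I error of about 8% to 26%. Nominal 95% intervals would cover about 92% to 74%, and correct intervals would be about 1.1 to 1.7 times as wide. These sizes rest wholly on assumed values. Smaller means or milder dispersion shrink them, and with no overdispersion the error is nil.

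Because section 2 names the three diseases in the aim, a reader might infer that half of the trial's main conclusion is at risk. The documents do not support that: morbidity is a secondary objective with explorative p-values, and the primary test, the hierarchical procedure and the sample size are untouched. The change is worth making but is not a condition for the trial's main result.

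**What to change.** Add one sentence to section 9.3.3 and carry it into the SAP: counts of repeated study-disease episodes are analysed by negative binomial regression, or by Poisson regression with robust standard errors by child, with the log of observed time as offset. The offset only makes explicit the person-time basis already used in section 9.3.1. This takes about one line of analysis code and alters no trial procedure or sample size. The only downside is somewhat wider intervals where counts are overdispersed.

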### **9.3.4 Pooled analysis**

Prior to this study a similar study (pilot) had been conducted in Katanga, DRC, and a similar study will be conducted in Goronyo, Nigeria. After finalizing the studies the data from the three studies will be pooled and analysed jointly with adjustment for the study location.

### **9.3.5 Statistical analysis plan and software**

A detailed statistical analysis plan (SAP) will be developed prior to the data analysis. Software used will be SAS for Windows, Version 9.2 or higher (SAS Institute, Cary, NC, USA) and STATA, Version 11 (StataCorp, College Station, Texas, USA).

## **10. QUALITY CONTROL**

### **10.1 Coordination**

A field research coordinator will be dedicated to ongoing supervision and monitoring of study implementation. Clinical procedures and data collection will be evaluated regularly by the FRC. Other QC measures will include daily review of patient records, observation of interviews and clinical procedures, and ongoing evaluation of malaria laboratory procedures according to standardised checklists.

The PI and OCBA epidemiologist will be present for the set up of the study site prior to implementation. They will also be available to conduct site visits every 3 months and make additional support visits as needed.

### **10.2 Diagnostics**

Malaria RDT: Routine quality control procedures will include close monitoring and supervision of RDT performance against standardized monitoring checklists and blood films collected on a monthly basis including 15 positives and 15 negative samples to be crosschecked by expert microscopy as per the MSF OCBA quality control protocol.

*P. Falciparum* in Uganda\* has a prevalence superior 85% while *P. Malariae*, *P. Ovale*, *P. Vivax* prevalence is inferior 15%. If RDT result is negative but still clinic suspicion, diagnosis will be confirmed by laboratory to ensure that all the species are diagnosed.

### **10.3 Staff, Training, and Supervision**

In addition to the FRC, the study will have a dedicated team, including medical doctor, nurses, study assistants (incl. collection of weight and height measurements, participant tracers, supplement dispenser, receptionist). Efforts will be made to identify and recruit local staff.

Prior to study implementation, the PI and OCBA epidemiologist in collaboration with OCA epidemiologist and or investigator, and with the FRC, will provide initial training and support in study methodology and implementation. Targeted training will be provided for specific team roles and responsibilities, including clinical diagnostic algorithms, proper use of the malaria RDT, and technique in conducting objective questionnaire interviews, and accurate weight and height measurements.

To assure quality control†, constant training, supervision and evaluation will be provided during all the study period for assuring good results.

In addition, staff will be briefed on the MSF ways of working, its role and mandate.

## **11. ETHICAL CONSIDERATIONS**

The study will be performed in accordance with ethical principles that have their origin in the Declaration of Helsinki and are consistent with International Conference on Harmonisation (ICH)/Good Clinical Practice (GCP) and all applicable regulatory requirements.

### **11.1 Treatment of participants**

#### **Confidentiality**

The medical examinations and the interviews will be performed in a private setting to ensure patient confidentiality. Patient data will only be accessible to the relevant clinical staff and not accessible to any unauthorized person. In further data processing, patient data will be pseudonymous, and identified only by the

---

\* Centre for Disease Control and Prevention (CDC). <http://www.cdc.gov/>

† A quality control sample in measurements is a standard procedure to repeating an x number of measurements, e.g. 10 children measured twice for weight, height and MUAC for finding mistakes doing the same measures with the same team. This type of training and evaluation is a standard practice. In surveys, it is included in the SMART programme giving the training results automatically.

study number.

### **Optimal medical treatment**

Patient management will be based at all times on their clinical condition, independent of participation in the study. Participation in the study will not, at anytime, preclude supplementary treatment or a change in therapy if clinically indicated. The well-being of the patient will always be prioritised over study participation.

The study does not interfere with routine care normally delivered to children presenting to the Kaabong OPD. Children requiring hospitalisation on presentation will not be recruited into the study, children who are acutely malnourished; they will be referred to MoH/AAH programme.

### **Burden on study participants:**

Individual study participants will be asked to attend for minimum 8 visits. A small compensation for time spent on travel and at the study clinic will be given after each scheduled clinical visit, e.g. a bar of soap. The incentives, or rather compensation (see annex f12 for incentive), are given after each visit to keep an interest of coming, to avoid suspicion that participation only cost only time and efforts. At the end of the study a larger compensation will be provided, e.g. blanket and salt. The total costs of the compensation will be equivalent to the market value of the approximate average duration of travel and time spend in the clinic for the research. This will be approximately 10 hours.

Choices for the products will be made in close collaboration with a diversity of stakeholders within the community (mothers, community health workers, District Health Officer) and in observation of market prices.

## **11.2 Cooperation with national and local partners**

Collaboration and cooperation between MSF-OCBA and Uganda health authorities is critical for the success of this study and uptake of results if positive outcomes are demonstrated. It will be essential to ensure access to and provision of study information to key policy in combating malnutrition. Permission to run the study will be obtained from the Uganda National Health Research Organisation (UNHRO). In addition, the local administrative authorities will be consulted about the nature and time-schedule of the planned study.

The details of the study and its implications will be discussed with all relevant stakeholders, at local and national levels. [name], the Kaabong DHO, will be assigned co-authorship to assure that there is local dissemination of study progress, the study results to the local participating community. Also [name] long term association with Kaabong aims to allow the study research to contribute to local research skill building

As the study involves a temporary intervention with a temporary benefit for those receiving an active intervention, it is essential that community members understand the purpose of the investigation and agree with the procedures. MSF-OCBA field visitors will consult with village chiefs and community members, especially targeting women with young children throughout the study to ensure understanding and ongoing community acceptance of the study.

